## Abstract

Background: Many women with breast cancer experience a great number of side effects, such as cognitive impairment, during and after chemotherapy that reduces their quality of life. Currently, research focusing on the use of non-pharmacological, and specifically telehealth interventions to prevent or mitigate them has been insufficient. Methods: This protocol describes a randomized controlled trial aimed at studying the preventive effects of a videoconferenced cognitive-adaptive training (e-OTCAT) program (ClinicalTrials.gov NCT04783402). A number of 98 eligible participants will be randomized to one of the following groups: (a) the experimental group receiving the e-OTCAT program during 12 consecutive weeks since the beginning of chemotherapy; and (b) the control group receiving and educational handbook and usual care. The primary outcome will be the cognitive function. Secondary measures will be psychological distress, fatigue, sleep disturbance, quality of life and occupational performance. The time-points for these measures will be placed at baseline, after 12 weeks and six months of post-randomization. Conclusion: This trial may support the inclusion of multidimensional interventions through a telehealth approach in a worldwide growing population suffering from breast cancer, emphasizing the prevention of cognitive impairment as one of the side effects of cancer and its treatments.

## 1. Introduction

Breast cancer (BC) and its treatments are accompanied by multiple consequences that need to be addressed [1], one of them being cognitive impairment [2].

The terminology to refer to this problem has evolved from *chemobrain* [3] to *cancer and/or chemotherapy related cognitive impairment* (CRCI) [4], after discovering that there are other factors related to cancer and its treatment that influence cognitive decline besides chemotherapy [5]. Nevertheless, patients undergoing chemotherapy have a higher chance of experiencing cognitive impairment [5]. The CRCI consists of an affection of the cognitive domains of attention, working memory and executive functions [6] that have an impact on patients’ daily lives and quality of life [7]. The incidence of CRCI among BC patients is approximately 33% in those treated with chemotherapy [8]. Relating to its prevalence, 60–70% of women who have received this treatment report cognitive complaints during and immediately after chemotherapy [9,10].

Despite its frequency, the responsible mechanisms of CRCI are not yet entirely clear, but they appear to be multifactorial. Aging is a major risk factor for cognitive decline and may enhance the neurotoxic effects of chemotherapy [11]. Other demographical and lifestyle factors are potential contributors of CRIC such as education, socioeconomic status, menopausal status, physical activity level, smoking or alcohol consumption and general health condition [11]. Psychological distress [12], fatigue [13], or sleep disorders [14], as a result of the treatment and the cancer itself, might also play a role in the onset and the course of cognitive decline. Meanwhile, some chemotherapeutic agents such as anthracyclines may induce oxidative stress, pro-inflammatory cytokine levels, and consequently brain injury and CRCI [15]. Taxane drugs used in other chemotherapy regimens have the ability to cross the blood brain barrier and directly induce central neurotoxicity, and therefore CRCI, through neuroinflammation, abnormal neurogenesis and neural apoptosis [16]. In this sense, we are facing a growing population with a high risk to suffer from a lengthy alteration in these areas.

On the other hand, telehealth approaches have become a promising and practiced more frequently among healthcare disciplines [17]. The delivery of remote interventions through digital technology has the potential to reduce economic, time-related and geographical constraints in healthcare systems [18]. Furthermore, telehealth is not a new perspective in cancer patients. Technological support such as web- or telephone-based interventions has been used in cancer rehabilitation, obtaining significant positive outcomes to ameliorate CRCI [19,20,21] and achieve an occupational performance as close as possible to that prior to cancer treatment [22]. This approach includes asynchronous or real-time interventions that might be combined to improve the quality of care. In addition, the current COVID-19 pandemic highlights the need for remote interventions to ensure supportive care for at-risk populations such as cancer patients [23].

We propose the e-OTCAT program, taking up the recommendation of a recent meta-analysis suggesting the testing of the effectiveness of interventions targeted to cognitive impairment in a preventive setting for BC patients scheduled for neurotoxic chemotherapy [24], as well as the potential of occupational therapy and the advantages of a telehealth approach. It will involve a telehealth cognitive-adaptive training to prevent CRCI in women with BC undergoing neurotoxic chemotherapy. The e-OTCAT program has been created to work in combination with the effects of cognitive training to enhance brain plasticity and to address other co-existing factors during this period such as psychological distress and fatigue, as well as occupational performance and quality of life.

We hypothesize that women with BC performing the e-OTCAT program simultaneously to the first course of chemotherapy will report less CRCI, better quality of life with other clinical variables, and better occupational performance than those receiving the usual care.

The main objective will be to study the preventive effects of the e-OTCAT program on CRCI, comparing the differences on the cognitive function between two groups of women with BC undergoing chemotherapy: the experimental group (EG) performing the e-OTCAT program for 12 weeks, starting at the same time as they begin the first course of chemotherapy, and the control group (CG) receiving the usual care.

Secondary objectives will be to investigate the immediate and medium-term effects of the e-OTCAT program on cognitive function, psychological distress, fatigue, sleep quality, quality of life and occupational performance in women with BC undergoing chemotherapy.

## 2. Materials and Methods

### 2.1. Study Design

We propose to carry out a single blinded randomized controlled trial. This study will be conducted by the CUIDATE research group (BIO-277 group) from the University of Granada. The trial is based in accordance with the Template for Intervention Description and Replication (TIDieR) checklist [25] and registered in ClinicalTrials.gov NCT04783402. Figure 1 shows the flow diagram of the study participants.

### 2.2. Participants

Participants will be recruited from the University Hospital of San Cecilio and the University Hospital of Virgen de las Nieves (Granada, Spain), referred by the oncologists and nurses in charge. Eligible women with BC scheduled to receive chemotherapy will be recruited if they meet the inclusion criteria as follows: (a) female BC who are going to start adjuvant or neoadjuvant chemotherapy, (b) stage I-III of BC, (c) age range 18–70 years old, (e) must be able to speak, read and write Spanish well to complete written and verbal assessment, neurocognitive tests and study sessions, and (f) must have basic phone skills. Women will be excluded if they have: (a) a history of cognitive, mental and/or physical disorder that may make participation in the study difficult, the completion of assessments and the performance of intervention i.e., Alzheimer disease, Parkinson’s disease, multiple sclerosis, schizophrenia, bipolar disorder, etc.); (b) a prior history of cancer or secondary diagnosis of cancer, (c) a prior history of chemotherapy, or (d) hearing or visual deficit.

### 2.3. Procedure

After checking the eligibility of participants and receiving detailed information from the study, women will be scheduled by a researcher for baseline assessment in the days prior to the start of chemotherapy treatment. Assessments will be carried out in the CUIDATE group facility by a researcher not involved in the implementation of the study intervention. Assessments will be developed at three time-points: at baseline just before chemotherapy (t0), 12-weeks (t1) and six-months (t2) post-randomization. The e-OTCAT program will be conducted during 12 consecutive weeks starting at the same time that women begin chemotherapy treatment. Figure 2 shows the time-points of the study.

Ethical approval has been obtained from the Committee of Biomedical Research Ethics of Andalucía (Granada, Spain) and it adheres to the principles of the Helsinki Declaration (2013 version) [26]. All eligible participants will be informed about the study orally and in writing and they will sign the informed consent if they agree to participate.

### 2.4. Outcome Measures

#### 2.4.1. Primary Outcome

##### Cognitive Function

The Functional Assessment of Cancer Therapy-Cognitive Function (FACT-Cog) version 3 [27] will be used to assess subjective cognitive function. The FACT-Cog comprises 37 questions to be scored from 0 (“never” or “nothing” to 4 “several times a day” or “very much”), and grouped into four subscales: perceived cognitive impairment, perceived cognitive abilities, impact of perceived cognitive impairment on QoL and comments from others about cognitive performance. Higher scores indicate better cognitive function. Cronbach’s α values for BC patients range from 0.71 to 0.93 [28]. The Spanish version of the scale will be used.

#### 2.4.2. Secondary Outcomes

##### Other Cognitive Function Measures

The Trail Making Test (TMT) will be used to assess psychomotor speed, attention skills (TMT-A), flexibility, attentional set-shifting and mental tracking (TMT-B) [29]. Smaller scores mean better results. The B/A ratio will be calculated as a measure of executive control. The TMT is recommended by the International Cancer and Cognition Task Force (ICCTF) to measure cognitive function in cancer patients for its adequate psychometric properties [30].

Two indexes of the Wechsler Adult Intelligence Scale (WAIS-IV) will be used: the Working Memory Index (WMI), comprising digit span and arithmetic subtests, and the Processing Speed Index (PSI), comprising symbol search and coding subtests [31]. WMI and PSI have high reliability, with a Cronbach’s α of 0.94 and 0.90, respectively [32]. The Spanish version of the subtests comprising the scale will be used.

##### Psychological Distress

The Hospital Anxiety and Depression Scale (HADS) will be used to assess anxiety and depression [33]. A total score of 8 or more in both subscales indicates a possible depression/anxiety condition. The HADS has been validated in BC patients. Reliability values for the full scale and the anxiety and depression subscales are 0.90, 0.85 and 0.84, respectively [34]. We will use its Spanish validation for this study.

##### Fatigue

The Piper Fatigue Scale-Revised (PFS-R) will be used to assess cancer-related fatigue grouped into four areas: behavioural, emotional, sensorial and cognitive [35]. Higher scores indicate the greater impact of fatigue. The scale has a Cronbach’s α from 0.87 to 0.89 [36]. The Spanish version of the PFS-R will be applied.

##### Sleep Quality

The Pittsburgh Sleep Quality Index (PSQI) will used to measure seven subjective domains of sleep: quality, latency duration, efficiency, disturbance, medication use and daytime dysfunction [37]. A total score of ≤5 indicates a “good sleeper”, while total scores of >5 indicate poor sleep quality. The PSQI has demonstrated a good reliability in the BC population [38]. The PSQI is validated in Spanish, so this version will be used.

##### Quality of Life

The European Organization for Research and Treatment of Cancer Quality of Life Questionnaire Core 30 (EORTC QLQ-C30) version 3.0 was used. The EORTC QLQ-C30 is grouped into functional scales (physical, role, cognitive, emotional and social), symptoms scales (fatigue, nausea and vomiting, pain, dyspnoea, sleep disturbance, appetite loss, constipation, diarrhoea and financial impact), and a global health status/quality of life scale [39]. Higher scores indicate a greater level of functioning, more symptoms and greater quality of life. The overall quality of life subscale has a Cronbach’s α of 0.89 [40]. The Spanish version of the EORTC QLQ-C30 scale will be applied.

##### Occupational Performance

The Canadian Occupational Performance Measure (COPM) will be used to assess daily activity performance and satisfaction with daily activities [41]. A mean total score for performance and satisfaction is obtained, and higher scores indicate greater performance and satisfaction. The COPM has great test-retest, interrater reliability, and convergent and divergent validity values [42]. This tool has been translated into the Spanish language, so this version will be used.

### 2.5. Intervention

Eligible women will be randomized to one of the following groups: (a) EG: receiving the e-OTCAT program; or (b) CG: receiving the usual care. Procedures for each group are described as follows:

**For EG**: Participants will receive the e-OTCAT program during 12 consecutive weeks, starting at the same time that they begin the first course of adjuvant or neoadjuvant chemotherapy. Each week will include two individualized sessions via videoconference using web conferencing software, conducted by a trained occupational therapist. Sessions will be organized as follows (see Table 1 for more detailed information):

***Cognitive training*** sessions will take place once a week (12 sessions) by videoconference (30′), where the participant will perform exercises to strengthen cognitive function in terms of attention, memory and processing speed. Besides this weekly session, each participant must complete a weekly series of cognitive training exercises at home. These will consist of an exercise using a handbook and paper and pencil and the mobile application of NeuroNation©, a German brain-training software company. We will encourage participants to complete a minimum of 20′ minutes per week of each homework modality.***Adaptive training*** sessions will take place also once a week since the second week to the second to last (10 sessions) through the videoconference, and it will be based on cognitive-behavioural techniques. Participants will train in the following areas: psychoeducation concerning stress management, relaxation techniques (diaphragmatic breathing, progressive muscle relaxation and differential relaxation), problem-solving training, and energy conservation techniques. After each session of adaptive training, participants will be motivated to practice the strategy seen in the session during the following days of the week until the next adaptive training session.

The therapist will monitor the adherence to homework cognitive training activities (mobile app and handbook) and adaptive strategies training through daily reports from the mobile app and self-registration for each activity.

**For CG**: Participants who are part of CG will receive standard care and an educational handbook containing general information about the most frequent side-effects of cancer and its treatment, most specifically about CRCI, psychological distress, cancer-related fatigue, sleep problems and lymphedema of the upper limbs. For ethical reasons, participants pertaining at CG could receive the e-OTCAT program when their participation in the study is completed.

### 2.6. Sample Size

The sample size for cognitive function was calculated based on a similar previous study using FACT-Cog version 3.0 [43]. Assuming an alpha error of 0.05, a power of 85% and a medium effect size (d = 0.58) based on the results of the reference study, we need a sample of 44 participants for each group (G*Power v.3.1). In order to compensate for a possible 10% dropout rate [44], we will recruit a total of 98 participants (49 per group).

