### 2.8. Statistical Analysis

The SPSS 25 software (IBM Statistic Program for the Social Sciences SPSS Statistic, Corp., Armonk, NY, USA) will be used for all data analyses. In all analyses, *p* < 0.05 values will be considered statistically significant. A blind researcher will perform the statistical analysis.

Descriptive statistics will be used to examine the sociodemographic and clinical characteristics of the sample. Data will be expressed as mean ± standard deviation (SD) or means (95% CI) for continuous, and as number or percentages for categorical variables. We will check the normal distribution of variables with the Kolmogorov-Smirnov test and visual inspection. Comparison between the two groups of the study (EG and CG) for baseline demographic data will be done with Student’s *t*-test for continuous, or a Chi-square test for categorical variables. Their non-parametric homologues, i.e., the Mann-Whitney U and Fisher’s exact test, will be used as appropriate.

Bivariate correlations will be used to explore the role of different variables that have been shown to determine cognitive performance in BC patients. Age and educational level will be considered as variables to be controlled for data analysis. Differences in cognitive function of participants receiving vs. not receiving the e-OTCAT program, as well as differences within-groups, will be calculated with a generalized linear mixed model. Substitution by means will be undertaken to treat the possible missing data. All analysis will be “intention-to-treat”. Calculation of the intergroup effect size (using Cohen’s d) will be performed to provide magnitude changes.

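### The 44 per group is the one-sided answer; at a two-sided 5% level the stated 85% power is about 77%

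*Protocol article*

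**What the plan says.** Section 2.6 of the protocol article gives the inputs as "Assuming an alpha error of 0.05, a power of 85% and a medium effect size (d = 0.58"), with the effect size taken from an earlier study that used the same questionnaire, FACT-Cog version 3. The result is "we need a sample of 44 participants for each group (G*Power v.3.1"). The dropout step follows: "In order to compensate for a possible 10% dropout rate [44], we will recruit a total of 98 participants (49 per group"). The section does not say whether the test is one-sided or two-sided, does not name the test selected in G*Power, and gives no correlation between baseline and follow-up.

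Section 2.8 sets a single significance rule for all analyses: p < "0.05 values will be considered statistically significant". The same section lists baseline comparisons by t-test and chi-square, descriptive reporting as "or means (95% CI) for continuous" variables, and the group comparison of cognitive function, which "will be calculated with a generalized linear mixed model". No one-sided test is declared for any of these. The hypothesis in the Introduction is worded in one direction (less cognitive impairment with the programme), while the objectives that follow it are worded neutrally.

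**The concern.** A standardised difference of 0.58 with 85% power at a two-sided 5% level needs clearly more than 44 per group, so the stated inputs and the stated result do not fit under the usual reading of alpha 0.05. If the calculation was run with one tail and the trial is read with two, the 85% is not the power of the test that will be reported.

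This concerns the primary outcome. A reader told that power is 85% will take a non-significant result as fairly strong evidence that an effect of 0.58 is absent. If the chance of missing such an effect is nearer one in four than one in seven, that inference is weaker than the article suggests.

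**Working it through.** **Inputs (section 2.6).** d = 0.58, alpha = 0.05, power = 85%, equal groups, 10% dropout.

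**Method.** Independent two-sample t-test with the noncentral t distribution, which is the G*Power calculation for two independent means. With n per group, df = 2n − 2 and the noncentrality parameter is d × √(n/2). Power is the probability that the noncentral t exceeds the critical value (in either direction for a two-sided test).

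**Reproducing the stated 44.** At n = 44, df = 86 and the noncentrality parameter is 0.58 × √22 = 2.720.

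| Test at alpha 0.05 | Critical t (df 86) | Power at n = 44 | n for 85% power |
|---|---|---|---|
| One-sided | 1.663 | 85.4% | 43.4, so 44 |
| Two-sided | 1.988 | 76.7% | 54.4, so 55 |

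One-sided power at 43 per group is 84.7%, so 44 is exactly the smallest one-sided sample size.

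**Cross-check by the normal approximation,** n = 2(z_alpha + z_power)² / d²:
- One-sided: 2 × (1.645 + 1.036)² / 0.58² = 42.7, so 43.
- Two-sided: 2 × (1.960 + 1.036)² / 0.58² = 53.4, so 54.

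Each is one below the t-based answer, as expected.

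**Could rounding or another simple test explain it?** Any d from 0.575 to 0.585 gives 54 to 56 per group two-sided. A Mann-Whitney test (efficiency 3/π under normality) gives 46 one-sided and 57 two-sided. Neither yields 44 two-sided.

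**Dropout step.** 44 / 0.9 = 48.9, so 49 per group and 98 in total. This is correct; the problem lies only in the 44.

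**Two-sided power at d = 0.58 for other numbers analysed.**

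| Analysed per group | Two-sided power |
|---|---|
| 39 (20% loss, assumed for illustration) | 71.5% |
| 44 (as planned after 10% loss) | 76.7% |
| 49 (no loss) | 81.1% |
| 55 | 85.4% |

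**Effect detectable.** With 44 per group, two-sided power reaches 85% at d = 0.646, about 0.65.

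**Size for a true two-sided 85%.** 55 evaluable per group; 55 / 0.9 = 61.1, so 62 recruited per group and 124 in total.

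**Effect of baseline adjustment (the correlation r is an assumption; the article gives none).** Adjustment multiplies the standard deviation by √(1 − r²), so the effective d is 0.58 / √(1 − r²). Reaching 0.646 needs r = √(1 − (0.58/0.646)²) = 0.44. With 44 per group, two-sided power is about 80.5% at r = 0.3, 85% at r = 0.44, 87% at r = 0.5 and 92% at r = 0.6.

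**The case against.** The strongest reply is that the article never says two-sided. The hypothesis is directional, a one-sided 5% calculation is consistent with it, and the 85% would then be correct. It is true that sidedness is inferred here. But a directional expectation is ordinary in a superiority trial and does not by itself make the test one-sided. Section 2.8 applies the same threshold to baseline and within-group comparisons, which nobody would read one-sided. The 95% intervals there are descriptive, so they give only mild support. If a one-sided 5% test was really intended, that is a consequential choice that has to be stated, so the text needs correcting either way.

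A second reply is that 77% is not the power of the planned analysis, which is a mixed model with age and educational level as variables to control. This stands in part. The 77% belongs to an unadjusted t-test at one time point, and a baseline-adjusted analysis could reach 85% or more. A repeated-measures or adjusted calculation with r around 0.4 to 0.45 would also give 43 to 45 per group two-sided (normal approximation), so the one-sided reading is the simplest explanation of the 44 rather than the only conceivable one. However, section 2.6 describes a plain Cohen's d calculation with no correlation, and section 2.8 does not say how baseline enters the model. The unstated correlation cannot be credited to the stated power.

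A third reply is that the shortfall is only about 4 points if nobody is lost. That is right for 49 per group (81.1%), but the article itself plans on 10% loss, and filling gaps by mean substitution adds no information.

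**Conclusion.** The figure is wrong as written. Under the unqualified 5% rule of section 2.8, read as two-sided, 44 per group gives 76.7% power for d = 0.58, about 8 points below the stated 85%. The type II error is about 23% instead of 15%. Among simple two-group t-tests, the 44 is exactly the one-sided answer, and the two-sided answer is 55.

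The conclusion assumes that the primary test will be read two-sided, that d = 0.58 is a between-group standardised difference, and that power is judged for an unadjusted comparison with 44 per group analysed. The arithmetic itself is not in doubt. The first assumption is the conventional reading, and nothing in the article declares otherwise.

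**What to change.** Keep the total at 98 and correct the wording.

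- **Section 2.8:** state that all tests are two-sided at the 5% level.
- **Section 2.6:** replace the power statement with: 'With 44 evaluable participants per group, a two-sided 5% t-test has 77% power to detect d = 0.58, and 85% power to detect d = 0.65.'
- **If the primary analysis adjusts for baseline FACT-Cog:** say so, and add that 85% power for d = 0.58 is regained with 44 per group if the correlation between baseline and 12-week FACT-Cog is at least about 0.44, with that correlation labelled as an assumption.

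If a one-sided test was in fact intended, the authors would have to declare and justify it in both sections.

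The cost is wording only, with no extra participants and no change to the design; the stated power becomes less favourable. Holding to 85% two-sided without relying on baseline adjustment would instead mean recruiting 62 per group (124 in total), 26 more than planned.
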